## Abstract

**Background:**

Novel strategies are required to increase school-based physical activity levels of children. Integrating physical activity in mathematics lessons may lead to improvements in students’ physical activity levels as well as enjoyment, engagement and learning. The primary aim of this study is to evaluate the impact of a curriculum-based physical activity integration program known as EASY Minds (Encouraging Activity to Stimulate Young Minds) on children’s daily school time physical activity levels. Secondary aims include exploring the impact of EASY Minds on their engagement and ‘on task’ behaviour in mathematics.

**Methods/Design:**

Grade 5/6 classes from eight public schools in New South Wales, Australia will be randomly allocated to intervention (n = 4) or control (n = 4) groups. Teachers from the intervention group will receive one day of professional development, a resource pack and asked to adapt their lessons to embed movement-based learning in their daily mathematics program in at least three lessons per week over a six week period. Intervention support will be provided via a weekly email and three lesson observations. The primary outcomes will be children’s physical activity levels (accelerometry) across both the school day and during mathematics lessons (moderate-to-vigorous physical activity and sedentary time). Children’s ‘on-task’ behaviour, enjoyment of mathematics and mathematics attainment will be assessed as secondary outcomes. A detailed process evaluation will be undertaken.

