**Flow of participants through the EASY Minds study**

### Sample size calculation

Power calculations were conducted to determine the sample size required to detect changes in the in the primary outcome of accelerometer-determined physical activity counts per minute (CPM) [27]. Calculations assumed baseline-posttest correlation scores of *r* = 0.30 and were based on 80% power, with alpha levels set at *p* < 0.05. Using the standard deviation (SD) of change observed in the EASY Minds pilot study (SD =200 CPM) and a conservative intra-class correlation coefficient (ICC = 0.15), it was calculated that a study sample of N = 200, with 8 clusters (i.e., schools) of 25 students would provide adequate power to detect a between group difference of 200 CPM across the school day.

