### Physical activity

The primary outcome will be children’s school-based PA levels. Actigraph accelerometers (GT3X, Pensacola, USA) will be used to provide an objective measure of both PA intensity and duration [30]. The Actigraph accelerometer has acceptable reliability and validity in both children and adolescents [31]. Accelerometers will be worn Monday through to Friday, during school hours only. This will vary slightly for each school setting as the schools are likely to have different start and finish times. The classroom teachers will receive training in how to instruct students to wear accelerometers and be responsible for distributing and collecting the accelerometers on a daily basis. Accelerometers will be attached to an adjustable elastic belt and worn on the right hip. Raw data from the accelerometer will be screened and analysed using Meter plus software version 4.7 which allows for time specific analysis to accurately analyse lesson- and school-time PA. Participants’ PA will be included for analysis if they wear the accelerometer for at least five school hours on any given day. Similarly, students will only be included in the analysis if they wear the accelerometer for 50 minutes of the 60 minute mathematic lessons. This time period may vary from school to school as a result of schools individual timetables. The Evenson cut-points will be used to classify activity as sedentary: (0–100 CPM, light (101–2295 CPM), moderate (2296–4011 CPM), vigorous 4012 - ∞ CPM ) or MVPA [32]. MVPA is a variable calculated by summing moderate and vigorous PA. Data will be collected in 15 second epochs and non-wear time will be defined as 20 minutes of consecutive zero’s [33].

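### The protocol contradicts itself on the primary outcome: the trial is sized for school-day counts per minute, while the abstract declares MVPA and sedentary time in two time windows

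*Protocol article*

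**What the plan says.** The protocol article describes the primary outcome in three places.

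- **Abstract, Methods/Design.** Primary outcomes, in the plural: children's activity by accelerometry "across both the school day and during mathematics lessons (moderate-to-vigorous physical activity and sedentary time". Crossing two measures with two windows gives four. CPM is not among them.
- **Sample size calculation.** One outcome, the "primary outcome of accelerometer-determined physical activity counts per minute (CPM". The target is a "between group difference of 200 CPM across the school day".
- **Outcomes, Physical activity.** "The primary outcome will be children’s school-based PA levels", in the singular, with no metric or window. The section goes on to intensity cut-points for sedentary time and MVPA, and to wear rules for the school day and for lessons. CPM appears there only as the unit of the cut-points; mean CPM is not defined as an outcome.

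The primary aim in the abstract concerns "children’s daily school time physical activity levels", and the Discussion repeats it. The Statistical methods section applies the same linear mixed models, with a group-by-time term, to all primary and secondary outcomes, and names no deciding test.

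**The concern.** Which outcome is primary, and whether the sample size was calculated for it, are matters for the protocol. Here the article addresses both and its answers are incompatible. An unseen analysis plan could not resolve this without overriding one of the sections.

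Two things are at stake. First, the only sample-size justification is for a variable that the abstract's list leaves out, and the outcomes on that list have none. Second, the candidates answer different questions. The intervention changes mathematics lessons directly, so lesson MVPA could rise while activity over the whole school day does not. Under the abstract's list that would be a primary success. Under the stated aim and the sample-size section, which both refer to the school day, it would not. The trial's conclusion would depend on which section is read.

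**Working it through.** **1. Does the stated N fit school-day CPM?**

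Inputs, all from the Sample size calculation section: difference 200 CPM; "standard deviation (SD) of change observed in the EASY Minds pilot study (SD =200 CPM"; "baseline-posttest correlation scores of *r* = 0.30"; "based on 80% power, with alpha levels set at *p* < 0.05"; ICC 0.15; 8 schools of 25, so 100 students per arm. A two-sided test is assumed, as sidedness is not stated.

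- Design effect = 1 + (25 − 1) × 0.15 = 4.6. Effective size per arm = 100 / 4.6 = 21.7.
- Total N = 2 × 4.6 × 2 × [SD × (1.960 + 0.842) / 200]².

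The text gives both an SD of change and a correlation, so three readings are possible:

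| Reading | SD used (CPM) | Total N for 80% power | Power at N = 200, normal | Power at N = 200, t on 6 df |
|---|---|---|---|---|
| (a) 200 is a single-occasion SD; change SD = 200 × √[2 × (1 − 0.30)] | 236.6 | 202.2 | 79.6% | 64.4% |
| (b) 200 is the SD of change, as worded | 200 | 144.4 | 90.9% | 78.4% |
| (c) 200 is a single-occasion SD, baseline-adjusted; 200 × √(1 − 0.30²) | 190.8 | 131.4 | 93.3% | 82.0% |

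The 6 df are 8 schools minus 2 arms. Reading (a) with the normal approximation returns the stated N almost exactly. Reading (b) with 6 df comes within 2 points of 80%. The calculation is therefore approximately reproducible for school-day CPM.

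**2. What can be said about the abstract's outcomes?**

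The document gives no SD, effect or ICC for MVPA or sedentary time in either window, so no power follows. As a scale only, assume 8 schools of 25 and take the ICC as unknown. The difference detectable with 80% power, in SDs of change, is 2.802 × √(2 × design effect / 100) under the normal approximation. With 6 df the multiplier is about 3.37.

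| Assumed ICC | Design effect | Normal | t on 6 df |
|---|---|---|---|
| 0.05 | 2.2 | 0.59 SD | 0.71 SD |
| 0.15 | 4.6 | 0.85 SD | 1.02 SD |
| 0.30 | 8.2 | 1.13 SD | 1.36 SD |

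Whether effects of that size are plausible for these outcomes cannot be judged from the document.

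**3. If any one of four primaries could carry the trial**

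This is a conditional figure, since no section states such a rule. With four tests at 0.05, the chance of at least one false positive is 1 − 0.95⁴ = 18.5% if the tests are independent, and tends to 5% as they become perfectly correlated. All four measures come from the same monitor, lesson time lies within the school day, and MVPA and sedentary time divide the same wear time. The tests are thus expected to be correlated and the rate to fall below 18.5%.

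**The case against.** The strongest reply is that the body of the protocol is coherent. The Sample size calculation section explicitly calls CPM the primary outcome, its school-day window matches the aim, and N is about right for it. On that view the abstract is loosely worded, and the general label in the outcomes section is compatible with either metric. Much of this stands: CPM is a declared primary outcome, and the arithmetic is not the problem. But the abstract's list is specific rather than loose, and the outcomes section neither defines mean CPM as an outcome nor ranks the measures, so the conflict remains.

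Three stronger readings are tempting and should not be drawn.

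- A reader might infer that the MVPA and sedentary-time outcomes are underpowered. The document shows only that no justification is given; their power is unknown.
- A reader might infer that the trial will claim success on whichever outcome is significant, with an 18.5% error rate. No section states that rule, independence is implausible, and a testing order may sit in an analysis plan that is not shown. Its absence here is not a fault.
- A reader might take four as a stated number. The abstract's parenthesis could qualify lessons only; the two-by-two reading is the more natural one, but it is a reading.

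The Discussion also criticises earlier work for measuring only the whole day and so missing the effect during the intervention period. That is a good reason to keep and report the lesson measures. It does not settle whether they are primary.

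**Conclusion.** The concern holds as an internal contradiction. The sample-size section and the abstract name different primary outcomes, the outcomes section does not decide between them, and the difference can change what the trial concludes. It needs correcting because a lesson-only effect would be a primary success under one section and not under others.

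The stated N is approximately sound for school-day CPM: power of 79.6% under reading (a) with the normal approximation and 78.4% under reading (b) with 6 df, although reading (a) with 6 df gives only 64.4%. For MVPA and sedentary time no figure can be given without inputs that the document lacks. The 5% to 18.5% range applies only if any one of four primaries could count as success.

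**What to change.** Name one primary outcome, in the same words, in the abstract, the Sample size calculation section and the Physical activity outcomes section: the between-group difference in change from baseline to post-test in mean school-day CPM, tested by the group-by-time term. This matches the aim, the existing calculation and the planned model. Define mean CPM in the outcomes section, and make school-day and lesson MVPA and sedentary time secondary.

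Alternatively, name school-day MVPA as the single primary outcome and redo the sample-size paragraph with its own SD, effect and ICC. The Background section reports pilot effects on MVPA and sedentary time in both windows, so the investigators may hold data for this, but N could change.

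The first option costs a few sentences of protocol wording, plus a check that the registry entry (not available here) agrees. The small downside is that fewer outcomes carry primary status; the lesson measures would still be analysed and reported.

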**Discussion:**

EASY Minds is an innovative intervention that has the potential to improve key physical and academic outcomes for primary school aged children and help guide policy and practice regarding the teaching of mathematics.

**Trial registration no:**

Australian and New Zealand Clinical Trials Register ACTRN12613000637741 13/05/2013.

## Background

Global estimates demonstrate that less than 20% of young people are achieving the guidelines of 60 minutes per day of ‘health enhancing’ moderate-to-vigorous physical activity (MVPA) [1]. This is of concern as multiple physical and psychological health benefits can be attained when children are physically active [2]. While schools have long been identified as important institutions for the promotion of physical activity (PA) among children [3, 4], children’s time at school is commonly characterised by low levels of PA. Moreover, children also experience prolonged bouts of sitting while at school [5]. Reducing sitting time or sedentary behaviour has important and independent health implications for children [6]. Studies have found that sedentary behaviour is associated with a higher risk of overweight [7], adverse metabolic markers [8] and poorer mental health [9]. Therefore, reducing sitting time and promoting physical activity across the school day may have important health benefits for children [10, 11].

The crowded school curriculum, competing demands on teachers, low levels of teacher expertise in PA promotion and restrictive school policies have impacted on both the quality and quantity of PA opportunities in primary schools [12, 13]. Indeed, educational researchers have stated that that the single biggest barrier to PA promotion are teachers’ own beliefs, perceptions and attitude towards PA [14]. Despite these challenges, schools provide an ideal setting in which changes can be implemented for facilitating PA opportunities and reducing sedentary behaviour [15]. However, novel strategies for PA promotion throughout the school day that are feasible and appealing for teachers and schools to implement are needed [12, 16, 17]. One such strategy is PA integration across the curriculum [4, 14, 18].

The potentially appealing aspect for teachers and schools of integrating PA across the school curriculum is that the benefits to children extend beyond the health benefits of physical activity [19, 20]. For example, recent research suggests that movement aids learning and that the integration of PA across the curriculum may enhance learning in other curriculum areas [20, 21]. This challenges the belief that schools need to increase academic time and reduce PA time to improve academic performance [22]. There is also an increasing body of literature that focusses on the association between PA and academic performance and provides evidence that PA enhances children’s cognitive functioning, concentration and on-task behaviour [23]. The integration of PA into other subjects may also enhance connectedness by providing real life application of academic concepts to enable students to view learning as significant and meaningful [24]. For example, in mathematics, using real stimuli such as stopwatches, tape measures, and trundle wheels to gather data provides a real life context and interactive teaching methods that promote movement, which are associated with greater learning [24].

The proposed program builds on a successful pilot of the EASY (Encouraging Activity to Stimulate Young) Minds program [25], where significant intervention effects were found for MVPA and sedentary time for the intervention group during mathematics lessons and across the whole school day. Furthermore, children displayed significantly greater ‘on-task’ behaviour across the intervention period. However, the pilot study research was carried out in a single school and all sessions were planned and delivered by a member of the research team.

## Methods/Design

### Study design

The EASY Minds program is a 6 week primary school-based intervention and will be evaluated using a cluster randomised controlled trial (RCT). Ethics approval has been sought and obtained from the University of Newcastle, NSW, Australia and the New South Wales Department for Education and Communities (SERAP: 2013011).The EASY Minds trial is registered with the Australian and New Zealand Clinical Trials Registry (ACTRN12613000637741).

Following the initial recruitment processes, all eligible participants will complete baseline assessments. The design, conduct and reporting of the EASY minds program will adhere to the Consolidation Standards of Reporting Trials (CONSORT) guidelines and the extension for a cluster randomised control trials (RCT) [26]. Principals, teachers and parents will need to provide written informed consent.

### Recruitment and study participants

Eight government public primary schools from the Hunter Region, NSW, Australia will be recruited to participate in the EASY minds RCT. Stage 3 classes (Grades 5 and 6) at the study schools will be invited to participate in the study. School principals will receive an initial letter followed by an email. Schools will be randomly selected from a list of primary schools within a 20 km radius from the University of Newcastle. Schools will then be matched on size and demographics using the participating schools index of community socio-educational advantage (ICSEA). The ICSEA value is determined based on family background information provided to schools directly by families and includes data relating to parental occupation, and the school education and non-school education levels they achieved.

Randomization will occur after baseline assessments. A simple computer algorithm will be used to randomly allocate schools to either control or the treatment conditions by an independent researcher not involved in the study. This method will ensure all schools have an equal likelihood of allocation into one of the two study arms. Trained research assistants will conduct all assessments and administer all student questionnaires. All researchers will complete training sessions prior to assessment to maintain consistency and where possible, the same assessors will be used at baseline and post-test. Figure 1 shows the flow of participants through the study.

**Figure 1 Fig1:**
[figure not shown]
**Flow of participants through the EASY Minds study**

### Sample size calculation

Power calculations were conducted to determine the sample size required to detect changes in the in the primary outcome of accelerometer-determined physical activity counts per minute (CPM) [27]. Calculations assumed baseline-posttest correlation scores of *r* = 0.30 and were based on 80% power, with alpha levels set at *p* < 0.05. Using the standard deviation (SD) of change observed in the EASY Minds pilot study (SD =200 CPM) and a conservative intra-class correlation coefficient (ICC = 0.15), it was calculated that a study sample of N = 200, with 8 clusters (i.e., schools) of 25 students would provide adequate power to detect a between group difference of 200 CPM across the school day.

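### The power statement pairs an SD of change with a baseline–posttest correlation that has no role beside it; with 8 schools and t on 6 df, power for 200 CPM is about 64–78%, not 80%

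*Protocol article*

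**What the plan says.** All the planning inputs are in the Sample size calculation section of the protocol article. The target is to "detect a between group difference of 200 CPM across the school day". Power is set at 80% and alpha at 0.05. A correlation of 0.30 between the two measurements of each child is assumed. The variability is described as the "standard deviation (SD) of change observed in the EASY Minds pilot study (SD =200 CPM"), while the ICC is taken as 0.15. The article's conclusion is that "it was calculated that a study sample of N = 200, with 8 clusters (i.e., schools) of 25 students would provide adequate power".

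Three other places matter:

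- The Abstract and the Recruitment and study participants section make the school the unit of allocation, 4 schools against 4.
- Statistical methods specifies a linear mixed model with group, time and group-by-time terms, adjusted for clustering. For two time points this is a comparison of change between arms.
- The Background says that "the pilot study research was carried out in a single school".

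**The concern.** An SD of change and a baseline–posttest correlation are alternative inputs for a comparison of change. The correlation is what converts a single-time SD into an SD of change; once the SD of change is known, it is not used again. Giving both leaves the reader unable to tell what the 200 CPM is, and the two meanings lead to different sample sizes and different power.

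In addition, four schools per arm leave 6 degrees of freedom for the between-arm comparison. The critical value is then 2.45, not 1.96, and a calculation on normal quantiles flatters the design.

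At stake is how a non-significant result would be read. If power for 200 CPM is nearer 64% than 80%, about one trial in three with a true effect of that size would miss significance, against the one in five that the article implies.

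**Working it through.** **Inputs.** From Sample size calculation: difference 200 CPM; SD 200 CPM; r = 0.30; ICC 0.15; 8 schools of 25; 80% power; alpha 0.05. From the Abstract: 4 schools per arm, so 100 children per arm. Assumed because not stated: two-sided test, equal school sizes, ICC applying to the change score.

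**Design effect.** 1 + (25 − 1) × 0.15 = 4.6.

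**Step 1: reproduce N = 200 with normal quantiles.** Unclustered n per arm = 2 × (SD × 2.8016 / 200)², where 2.8016 = 1.960 + 0.842. Multiply by 4.6 and by 2 arms.

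- *200 as the SD of change, as labelled:* 2 × 2.8016² = 15.70 per arm; 15.70 × 4.6 × 2 ≈ 144.
- *200 as a single-time SD:* SD of change = 200 × √(2 × (1 − 0.30)) = 236.6; n = 21.98 per arm; 21.98 × 4.6 × 2 ≈ 202.

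The second reading uses r and lands within about 1% of the published 200. Its normal-approximation power at N = 200 is 79.6%. The first reading does not use r, and at N = 200 its normal-approximation power is 90.9%.

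**Step 2: allow for 8 schools.** SE = SD × √(2 × 4.6 / 100); noncentrality = 200 / SE; degrees of freedom = 8 − 2 = 6; critical t = 2.447.

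| Meaning of 200 CPM | SD of change | SE | Noncentrality | Power, normal | Power, t on 6 df | Detectable with 80% power, t on 6 df |
|---|---|---|---|---|---|---|
| SD of change | 200 | 60.7 | 3.30 | 90.9% | 78.4% | 204 CPM |
| Single-time SD | 236.6 | 71.8 | 2.79 | 79.6% | 64.4% | 242 CPM |

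Simulating school means and applying the 6-df t test gave 78.3% and 64.5%.

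**Step 3: sensitivity case on an added assumption.** If the pilot SD holds only within-school variance because the pilot had one school, and the ICC of 0.15 applies, total SD = SD / √0.85. The two SDs of change become 216.9 and 256.7, and power on 6 df becomes 71.8% and 57.6%, with detectable differences of about 222 and 262 CPM. The article does not say how its pilot SD relates to the total variance, so this shows sensitivity and is not a result of the stated inputs.

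**The case against.** The strongest defence is that the text should be taken at its word. It says SD of change. On that reading, 200 children exceed the roughly 144 that the standard formula needs, and the sentence claims only that the design is adequate, not that 200 is the minimum. Even on 6 df the shortfall is under 2 points, and an ICC of 0.14 instead of 0.15 would give 80.4%. That is within planning error for an ICC the authors call conservative. This stands: on the literal reading the gap has no practical weight. It does not explain what r = 0.30 was for, and the reading that uses r and comes close to N = 200 is the one with 64% power.

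A second defence is that r could enter through baseline adjustment. With t on 6 df, an ANCOVA would have about 82% power if 200 is a single-time SD (residual SD 200 × √(1 − 0.30²) = 190.8) and about 92% if it is the SD of change. So 78% is not a ceiling for every possible analysis. Statistical methods, however, specifies a group-by-time model, not a baseline-adjusted one.

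A reader might go further and infer that the authors ignored clustering. The documents do not support that: the number of schools, their size and the ICC are all stated, and the design effect of 4.6 is needed to come near N = 200. What appears to be missing is only the small-sample t allowance.

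**Conclusion.** The stated inputs are not coherent with one another, and the stated 80% is not reached on either change-score reading once the 8 schools are allowed for. Power for 200 CPM is about 78% if 200 is the SD of change and about 64% if it is a single-time SD. The shortfall is material only in the second case, and the paragraph does not let the reader tell which case applies.

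This rests on a two-sided 5% test, equal schools of 25, an ICC of 0.15 on change, and 6 degrees of freedom.

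Two stronger conclusions are tempting. One is that N = 200 was certainly derived from a single-time SD; the match at 202 makes this likely, but the article does not show its route. The other is that true power is as low as 58%; that figure needs the single-school assumption of Step 3 and does not follow from the printed inputs.

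**What to change.** Rewrite the Sample size calculation paragraph:

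1. Say whether 200 CPM is the SD of change or the SD of a single measurement. Drop r if it is the SD of change; if it is a single-time SD, show the conversion to 236.6.
2. Recompute with t on 6 df, and state that the test is two-sided if that is intended.
3. Report the resulting power for 200 CPM (about 78% or about 64%) or the difference detectable with 80% power (about 204 or about 242 CPM).
4. Note that the SD comes from a single-school pilot, with the 72% and 58% figures as a labelled sensitivity case if wanted.

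The cost is one recalculation and a reworded paragraph, with a less favourable power statement. The design, the number of schools and the analysis model stay as they are.
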